# 1 Protocol Summary

## 1.1 Synopsis

| **Title:** | TranExamic Atomized for Pediatric post-Operative Tonsillectomy hemorrhage: A Pilot and Feasiblity Study |  |  |  |
| --- | --- | --- | --- | --- |
| **Study Description:** | This study starts as single site pilot study, randomized, double-blinded controlled trial for 12 patients. Then dependent on funding, the study will be a multi-center, randomized, double-blinded, placebo-controlled trial. It is a parallel arms pilot trial randomizing up to 30 patients. |  |  |  |
| **Objectives:** | \| Primary Objective: \| The primary objectives of this pilot study are:   1. Enroll 0.6 patient's/site/month with PTH and 2. Evaluate the ability to nebulize at least two doses of TXA to children with PTH and 3. Determine the indirect local and systematic concentrations of nebulized TXA in children 4. Adverse events will be assessed 30 +/- 5 days from randomization \| \| \| \| --- \| --- \| --- \| --- \| \| Secondary Objectives: \| The secondary objectives of this pilot study are:   1. Determine the number and rationale for PTH patients to return to the OR; and 2. Determine the number of blood transfusions and estimated blood loss and 3. Determine the recurrence of PTH after TXA, saline or return to the OR. \| \| \| \| Exploratory Objectives: \| \| Establish pain and anxiety inventory at 7 +/- 1 from randomization. \| | | |  |
| **Endpoints:** | \| Primary Endpoint: \| Enrollment after one year, % of nebulization administered to patient's enrolled, and collection of two blood samples from each participant. Adverse events will be assessed at 30 +/- 5 days from randomization. \| \| --- \| --- \| \| Secondary Endpoints: \| Collection of surveys on ENT decision to go to the OR, electronic health record data on blood transfusions and estimated blood loss, and if PTH recurrences within seven days of randomization. \| \| Exploratory Endpoints: \| Age-appropriate pain and anxiety states at 7 +/- 1 days after randomization. \| | | | |
| **Study Population:** | Children aged 2 to 17 years old that present with post-tonsillectomy hemorrhage (PTH), ENT clinicians, parents of the children enrolled and missed eligible. | |  |  |
| **Phase:** | 2 | |  |  |

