# 3 Objectives and Endpoints

| OBJECTIVES | ENDPOINTS | JUSTIFICATION FOR ENDPOINTS |
| --- | --- | --- |
| Primary | | |
| Evaluate the feasibility to enroll 0.6 patients/site/month  Nebulize at least two of three doses of TXA to children with PTH.  Determine the local and systematic concentrations of nebulized TXA in children  Determine incidence of adverse and serious adverse events | Enrollment after one year and % of nebulization’s. Go/no-go threshold is 0.6 patients per site per month for a total of 22 patients. Time and success to obtain consent will establish need for exception for informed consent (EFIC).    The goal is >90% of patients will receive at least two of three planned nebulization of TXA.  Collection of two blood samples from each participant. This will verify a pulmonary physiological-based PK model (PBPK) (i.e., nasal cavity, pharynx, and lung) that indirectly predicts the oropharyngeal and systematic concentration of nebulized TXA.  A phone call or email will be placed to participants at 30 +/- 5 days. | The overall incidence of PTH is 5%, yet numbers per site may be very different. Assessment and consent will optimize site selection, recruitment process, and the plan the main trial.    The establishment of a pragmatic protocol design will help design a large trial.  Limited data on nebulized TXA systematic absorption. Topical PK studies of TXA document a significant reduction in systematic levels but the same hemostasis effect.  Safety Evaluation as recommended by the FDA. |
| Secondary | | |
| Determine the number and rationale for PTH patients to return to the OR; and    Determine the number of blood transfusions and estimated blood loss and      Determine the recurrence of PTH after TXA, saline, or return to the OR. | Collection number participants and surveys on ENT surgeons’ decision to go to the OR    Collection of electronic health record data on number of blood transfusions and estimated blood loss    Survey families to determine PTH recurred seven days from randomization. | To evaluate if return to the OR can be an outcome for the main trial.    To evaluate if TXA decreased severity of PTH bleeding.      To evaluate if TXA or return to OR prevented PTH recurrence. |
| Tertiary/Exploratory | | |

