## 7.2 Participant Discontinuation/Withdrawal from the Study

Participants are free to withdraw from participation in the study at any time upon request. A site investigator may discontinue or withdraw a participant from the study for the following reasons:

1. If any clinical adverse event (AE), laboratory abnormality, or other medical condition or situation occurs such that continued participation in the study would not be in the best interest of the participant.
2. Emergent intubation for respiratory failure.
3. If the participant meets an exclusion criterion (either newly developed or not previously recognized) that precludes further study participation.

The reason for participant discontinuation or withdrawal from the study will be recorded on the Adverse Event Case Report Form. Subjects who sign the informed consent form and are randomized but do not receive the study intervention may be replaced.  Subjects who sign the informed consent form, are randomized, and receive the study intervention, and later withdraw or are discontinued from the study, will no longer have data collected, but existing data collected prior to withdrawal will still be used. Subjects may be replaced as necessary depending about withdrawal.

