## 8.2 Safety and Other Assessments

## 8.2.1 Safety OUTCOMES

Incidence of safety outcomes will be assessed at 1, 7 and 30 days after receipt of the study drug via a review of electronic health records and interviews. Specific, safety outcomes are thromboembolic disease: any venous or arterial thrombosis on standard diagnostic imaging post-randomization (including deep vein thrombosis, pulmonary embolism, sinus thrombosis, myocardial infarction, ischemic stroke) and seizures occurring within 24 hours (greater than 5 half-lives of TXA) of drugs documented by clinical or electroencephalogram.

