### 8.3.4 Time Period and Frequency for Event Assessment and Follow-Up

The occurrence of an adverse event (AE) or serious adverse event (SAE) may come to the attention of study personnel during study visits and interviews of a study participant presenting for medical care, or upon review by a study monitor. All serious, unexpected, and related adverse events that are unresolved at the time of the subject's termination from the study will be followed by the Clinical Center investigators until the events are resolved, the subject is lost to follow-up, the adverse event is otherwise explained, or has stabilized.

All AEs including local and systemic reactions not meeting the criteria for SAEs will be captured on the appropriate case report form (CRF). Information to be collected includes event description, time of onset, clinician's assessment of severity, relationship to study product (assessed only by those with the training and authority to make a diagnosis), and time of resolution/stabilization of the event. All AEs occurring while on study must be documented appropriately regardless of relationship. All AEs will be followed to an adequate resolution.

Any medical condition that is present at the time that the participant is screened will be considered as a baseline and not reported as an AE. However, if the study participant's condition deteriorates at any time during the study, it will be recorded as an AE.

Changes in the severity of an AE will be documented to allow an assessment of the duration of the event at each level of severity to be performed. AEs characterized as intermittent require documentation of onset and duration of each episode.

Study staff will record all reportable events with start dates occurring any time after informed consent is obtained for 24 hours for non-serious AEs and 7 days for SAEs after randomization and at the 30-day (+/- 5 days) follow-up phone call for any AEs.  At each study visit, the investigator will inquire about the occurrence of AE/SAEs since the last visit.  Events will be followed for outcome information until resolution or stabilization.

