### 8.3.5 Adverse Event Reporting

Assuring patient safety is an essential component of this protocol. Each participating site investigator will have primary responsibility for the safety of the individual patients under his or her care. All adverse events occurring after study randomization for 30 days (+/- 5 days) will be recorded and entered the electronic data entry system into UTHSCSA REDCap for single site study and to the REDCap Database provided by the DCC for the multisite study. In accordance with local IRB requirements, the site investigator may be required to report such events to the IRB in addition to notifying the DCC.

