### 9.4.4 Safety Analyses

Incidences of seizure or thromboembolic events will be recorded for up to 30 (+/-5) days after receipt of study drug to be collected by e-mail, phone, or text for discharged patients and by chart review for patients who remain in the hospital. Differences in safety outcomes will be analyzed by unpaired t-tests (for ratio measures such as blood loss) or by Mann-Whitney tests.

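### Adverse-event incidence is a primary objective, but its collection windows conflict, and follow-up stops for treated children whom an investigator withdraws after a poor course

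*Protocol*

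**What the plan says.** **Status of the endpoint.** The Synopsis lists, among the primary endpoints, "Adverse events will be assessed at 30 +/- 5 days from randomization". The primary block of Section 3 includes "Determine incidence of adverse and serious adverse events". Section 8.1 names only enrolment rate and dose delivery as primary feasibility outcomes and adds that safety is always an outcome. The primary status of adverse events therefore rests on the Synopsis and Section 3.

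**Collection window.** Section 8.3.4 tells staff to record events that start after consent "for 24 hours for non-serious AEs and 7 days for SAEs after randomization and at the 30-day (+/- 5 days) follow-up phone call"; the sentence ends by saying that the call covers any adverse event. The same section requires all events on study to be documented and asks the investigator to inquire at each visit. Section 8.3.5 states: "All adverse events occurring after study randomization for 30 days (+/- 5 days) will be recorded". The Schedule of Activities marks adverse events at day 0-1, day 7 and day 30, and Section 8.2.1 assesses safety at days 1, 7 and 30.

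**Seizure.** Section 8.2.1 lists "seizures occurring within 24 hours (greater than 5 half-lives of TXA" as a specific safety outcome. Section 9.4.4 states: "Incidences of seizure or thromboembolic events will be recorded for up to 30 (+/-5) days after receipt of study drug".

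**Withdrawal.** Section 7.2 lets a site investigator withdraw a participant for, among other reasons, an adverse event or emergent intubation. Treated participants who withdraw or are discontinued from the study "will no longer have data collected, but existing data collected prior to withdrawal will still be used".

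**Analysis.** Section 9.4.4 states: "Differences in safety outcomes will be analyzed by unpaired t-tests (for ratio measures such as blood loss) or by Mann-Whitney tests". Section 9.4.1 says that safety outcomes will be described.

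**The concern.** An incidence needs one definition of what counts and over what period. Here a site that follows the restrictive sentence in 8.3.4 and a site that follows 8.3.5 can handle the same event differently, and two analysts can report different seizure counts from the same records. The protocol's own background (Section 2.2) describes delayed-onset adverse events, seizures among them, with intravenous tranexamic acid. A 24-hour count and a 30-day count therefore answer different questions.

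The withdrawal rule is a separate problem. It ends follow-up for reasons tied to the child's clinical course, so the missing safety data are related to the outcome being measured. The arms are planned at 6 children each in the single-site stage and 11 each in the multi-site stage, and the results are meant to inform a phase 3 design. In a trial of that size each child's safety record matters.

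**Working it through.** The plan gives no sample size, power or expected rate for adverse events, so there is no figure to reproduce. The check is mainly a comparison of the texts.

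**1. Length of the windows.** Taking the restrictive sentence in 8.3.4 by itself, before the day-30 call:
- non-serious events: 1/30 days = 3%
- serious events: 7/30 days = 23%
- both types under 8.3.5: 30/30 days = 100%

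**2. The same events under each rule.**

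| Event | Restrictive sentence in 8.3.4 | Rest of 8.3.4 | 8.3.5 |
|---|---|---|---|
| Non-serious, day 3, reported at day 7 | Outside 24 hours; recordable only through the day-30 call | Asked at day 7 and documented | Recorded |
| Serious, onset day 10 | Outside 7 days; recordable only through the day-30 call | Documented | Recorded |

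A seizure on day 3 is outside the safety outcome in 8.2.1 and inside the incidence in 9.4.4.

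Other texts also disagree on duration. Section 5.5 describes one week of outpatient follow-up, Section 4.4 gives 7 to 30 days, and the Synopsis gives thirty days. The start point differs too (consent in 8.3.4, randomization in 8.3.5), but Section 4.1 randomizes at the time of consent, so this has little effect.

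**3. What 7.2 keeps and loses.** Take a treated child whom the investigator withdraws after emergent intubation.
- Kept: all earlier data, and the reason for withdrawal, which goes on the adverse-event form (7.2).
- Followed: serious events already known, to resolution (8.3.6). Section 8.3.4 says that all adverse events are followed to resolution, but elsewhere limits follow-up after termination to unresolved events that are serious, unexpected and related.
- Lost: any new event after withdrawal, the day-7 outcomes (surgical control, recurrence, pain, anxiety) and the day-30 adverse-event call.

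Section 7.1 keeps children in the study when only the drug is stopped. It does not cover a child taken off the study.

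**4. Method in 9.4.4 (minor).** The named outcomes, seizure and thromboembolism, are yes/no. The sentence offers t-tests, tied to ratio measures, or Mann-Whitney, and nothing for a proportion. On 0/1 data Mann-Whitney is close to a chi-square test. At nominal 0.05 with 6 per arm, its exact type I error is 0.024 if the true event rate is 0.3, and 0.0001 to 0.039 for rates from 0.05 to 0.5 (all rates assumed). With 11 per arm the range is 0.002 to 0.053. It is poorly suited rather than invalid.

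If no events occur, Mann-Whitney returns p = 1. The informative figure is the one-sided exact 95% upper limit, 1 - 0.05^(1/n):
- 0/6: 1 - 0.05^(1/6) = 0.39
- 0/11: 1 - 0.05^(1/11) = 0.24

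**The case against.** **The contacts already exist.** Adverse events are asked about at days 7 and 30, 8.3.4 itself requires all events on study to be documented, and 8.3.6 requires immediate reporting of any serious event. A reader might infer that a non-serious event on day 3 is simply lost. The text does not support that: it is asked for at day 7 and again at the day-30 call. What stands is narrower. One sentence conflicts with its own section and with 8.3.5, and a site that follows it would leave later non-serious events to recall at day 30.

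**Seizure.** The 24-hour outcome could be a special-interest definition within a 30-day recording period. That is possible, and a late seizure would still be recorded under 8.3.5 and 9.4.4. The protocol does not say that this is intended, so which count is the reported incidence stays open.

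**Withdrawal.** It is discretionary, the triggering event is kept and known events are followed. A reader might infer that each withdrawn child removes an event and so shifts incidence by 1/6 = 17 or 1/11 = 9 percentage points. That does not follow: a child withdrawn for a recorded adverse event is already a case. The loss is of new events and later outcomes.

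**Tests.** A reader might infer that t-tests are assigned to seizures or thromboembolism. They are not: 9.4.4 ties the t-test to ratio measures, and 9.4.1 makes safety descriptive. Methods for proportions may also sit in an analysis plan that is not shown, and the 39% and 24% limits reflect sample size, which no analysis method changes. This leaves only a minor mismatch in 9.4.4.

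**Conclusion.** The point holds on two counts. First, the collection rules for a primary safety objective contradict each other: 24 hours and 7 days plus a call in one sentence of 8.3.4, against all events to day 30 in 8.3.5 and elsewhere in 8.3.4, and 24 hours against 30 days for seizure. Second, 7.2 ends data collection for treated children whom an investigator withdraws for an adverse event or emergent intubation, so new events and the day-7 and day-30 outcomes go missing for reasons related to the child's course.

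The size is partly fixed by the text: 1 or 7 of 30 days against 30 of 30, if the restrictive sentence is applied alone. The effect on incidence cannot be computed, because the protocol gives neither expected event rates nor an expected number of investigator withdrawals. The existing contacts at days 7 and 30 limit the damage from the first problem. They do not help with the second, because withdrawn children no longer have those contacts. The method mismatch in 9.4.4 is minor. The changes should be made, but nothing here undermines the trial's design.

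**What to change.** 1. **One window** in 8.2.1, 8.3.4, 8.3.5 and 9.4.4: all adverse and serious adverse events, seizures included, from randomization to day 30 (+/-5), asked at the existing contacts. Report seizures within 24 hours as a subset. Align the follow-up lengths in 4.4 and 5.5 with this.
2. **Section 7.2:** end data collection only when the family withdraws permission. After investigator-initiated withdrawal, continue chart and phone safety follow-up to day 30.
3. **Section 9.4.4 (minor):** report the number of children with each yes/no event by arm with exact confidence intervals, in keeping with the descriptive approach in 9.4.1. Leave the named tests to measures such as blood loss.

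The cost is protocol and case-report-form wording. The day-7 and day-30 contacts are already scheduled, so no visit is added. The downside is a few more non-serious events to record.

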### 8.3.5 Adverse Event Reporting

Assuring patient safety is an essential component of this protocol. Each participating site investigator will have primary responsibility for the safety of the individual patients under his or her care. All adverse events occurring after study randomization for 30 days (+/- 5 days) will be recorded and entered the electronic data entry system into UTHSCSA REDCap for single site study and to the REDCap Database provided by the DCC for the multisite study. In accordance with local IRB requirements, the site investigator may be required to report such events to the IRB in addition to notifying the DCC.

### 8.3.6 Serious Adverse Event Reporting

The study clinician will immediately report to the sponsor any serious adverse event, whether considered study intervention-related, including those listed in the protocol or investigator brochure, and must include an assessment of whether there is a reasonable possibility that the study intervention caused the event. Study endpoints that are serious adverse events (e.g., all-cause mortality) must be reported by following the protocol unless there is evidence suggesting a causal relationship between the study intervention and the event (e.g., death from anaphylaxis). In that case, the investigator must immediately report the event to the sponsor.

All serious adverse events (SAEs) will be followed until satisfactory resolution or until the site investigator deems the event to be chronic or the participant is stable. Other supporting documentation of the event may be requested by the Data Coordinating Center (DCC)/study sponsor and should be provided as soon as possible.

The study sponsor will be responsible for notifying the Food and Drug Administration (FDA) of any unexpected fatal or life-threatening suspected adverse reaction as soon as possible, but in no case later than 7 calendar days after the sponsor's initial receipt of the information. In addition, the sponsor must notify FDA and all participating investigators in an Investigational New Drug (IND) safety report of potentially serious risks, from clinical trials or any other source, as soon as possible, but in no case later than 15 calendar days after the sponsor determines that the information qualifies for reporting.

### 8.3.7 Reporting Events to Participants

All serious, unexpected, and related adverse events that are unresolved at the time of the patient's termination from the study or discharge from the hospital will be followed by the Clinical Center investigators until the events are resolved, the patient is lost to follow-up, the adverse event is otherwise explained or has stabilized.

## 8.4 Unanticipated Problems

### 8.4.1 Definition of Unanticipated Problems (UP)

The Office for Human Research Protections (OHRP) considers unanticipated problems involving risks to participants or others to include, in general, any incident, experience, or outcome that meets **all** the following criteria:

A. Unexpected in terms of nature, severity, or frequency is given (a) the research procedures that are described in the protocol-related documents, such as the institutional Review Board (IRB)-approved research protocol and informed consent document; and (b) the characteristics of the participant population being studied.

B. Related or possibly related to participation in the research (“possibly related” means there is a reasonable possibility that the incident, experience, or outcome may have been caused by the procedures involved in the research); and

C. Suggests that the research places participants or others at a greater risk of harm (including physical, psychological, economic, or social harm) than was previously known or recognized.

### 8.4.2 Unanticipated Problem Reporting

The investigator will report unanticipated problems (UPs) to the reviewing Institutional Review Board (IRB) and to the Data Coordinating Center (DCC)/lead principal investigator (PI). The UP report will include the following information:

A. Protocol identifying information: protocol title and number, PI's name, and the IRB project number.

B. A detailed description of the event, incident, experience, or outcome.

C. An explanation of the basis for determining that the event, incident, experience, or outcome represents a UP;

D. A description of any changes to the protocol or other corrective actions that have been taken or are proposed in response to the UP.

To satisfy the requirement for prompt reporting, UPs will be reported using the following timeline:

A. UPs that are serious adverse events (SAEs) will be reported to the IRB and to the DCC/study sponsor within a timeline in accordance with the policy of the investigator becoming aware of the event.

B. Any other UP will be reported to the IRB and to the DCC/study sponsor within the timeline in accordance with the policy of the investigator becoming aware of the problem.

C. All UPs should be reported to appropriate institutional officials (as required by an institution's written reporting procedures), the supporting agency head (or designee), and the Office for Human Research Protections (OHRP) within a timeline in accordance with policy, of the IRB's receipt of the report of the problem from the investigator.

